## Introduction

Worldwide, liver cirrhosis ranks as the 11th most common cause of death. In 2019, it accounted for an estimated 1.48 million deaths, reflecting an 8.1% increase since 2017 [1]. The distribution of cirrhosis etiologies and their prevalence varies across countries, largely due to differences in lifestyle factors such as alcohol consumption, obesity, and the risk of viral hepatitis. In Europe, alcohol-related liver disease (ARLD) is currently the leading cause of cirrhosis-related deaths [2].

Liver cirrhosis is the end stage of chronic liver disease of all causes, resulting from sustained inflammation that progresses to fibrosis and, ultimately, liver failure. The progression of liver cirrhosis is divided into a compensated stage, characterized by an absence of specific symptoms and apparent complications, and a decompensated stage featuring one or more severe complications such as ascites, hepatic encephalopathy, infection, renal dysfunction, and variceal bleeding [3]. At this stage, the patient often experiences fatigue, nausea, malnutrition and increasing frailty due to loss of muscle mass. This transition from compensated to decompensated liver cirrhosis significantly worsens health-related quality of life (HRQoL) scores [4, 5], while median survival decreases dramatically from approximately 12 years to just two years [6, 7]. Patients with decompensated liver cirrhosis experience some of the highest rates of unplanned hospital admissions, with 1.5 to 3 liver-related admissions per year [8–12].

The current management of decompensated liver cirrhosis focus on symptom relief, the prevention of further complications, and, if possible, liver transplantation, which remains the only curative option [7–14]. According to the World Health Organization, palliative care should be integrated alongside life-prolonging medical treatment as part of a cohesive approach to care, focusing on enhancing the quality of life for patients and their informal caregivers facing the challenges of serious illnesses. Palliative care aims to prevent and relieve suffering through early identification, assessment, and treatment of physical, psychosocial, and spiritual symptoms and concerns [15].

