### Intervention elements

The intervention is delivered alongside standard care and integrated into patients’ regular clinical appointments. In all participating settings, standard care involves routine follow-up of patients with cirrhosis by a team of hepatologists and specialised liver nurses. Following an admission due to decompensated cirrhosis, patients are routinely offered planned follow-up in an outpatient clinic.

The initial palliative care conversation is conducted by a hepatologist in collaboration with a specialised liver nurse. Alternatively, the conversation may be conducted solely by the liver nurse. Subsequent conversations are conducted by either a hepatologist or a liver nurse after 4–10 weeks, and at 6, 12, 18, 24, 30, and 36 months, or until withdrawal from the study or death. Extra visits may be scheduled if clinically indicated or if the patient or informal caregivers request additional support or planning.

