### Effectiveness outcomes

#### Primary outcome

*Healthcare system burden*, measured as the number and length of hospital admissions from the initial visit to death or study exit. Data on health care utilisation will be prospectively recorded by registering events since the last visit at each study visit and compared to a recent historic cohort of a similar size from the involved centers.

Hospital admissions will be categorised into three mutually exclusive groups:

*Liver-related admissions*: inpatient stays of ≥ 24 h due to complications of liver cirrhosis, including variceal bleeding and other bleeding related to portal hypertension, hepatic encephalopathy, spontaneous bacterial peritonitis, hepatorenal syndrome, alcoholic hepatitis, ascites, infection, electrolyte imbalances, increasing frailty, sarcopenia, or poor nutritional status.*Non-liver-related admissions*: inpatient stays of ≥ 24 h for conditions not directly related to cirrhosis.*Short admissions*: hospital stays of < 24 h, excluding admissions in which paracentesis is the sole intervention.

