## Sample size and statistical methods

### Sample size

The study aims to include 240 patients and 100 informal caregivers, based on sample size calculations for the most significant outcomes and to accommodate expected attrition.

The Healthcare System Burden will be measured as the number and length of admissions. Patients with cirrhosis spend an average of seven days per year in hospital [39]. Health care utilization data from the intervention group will be compared to a recent historical cirrhosis cohort. For the sample size calculation, we assumed the historical cohort will have an average of seven days in hospital per year and hypothesize that the intervention will cause a reduction of two days/year with an assumed SD of 7 days. Hence, 199 participants are required (STATA BE 18.5). With an estimated attrition rate of 20%, we aim to include 240 patients [40, 41].

Caregiver burden will be measured using the 22-item ZBI (range 0–88). A change of 5 points is considered realistic and clinically relevant. Based on previous studies, this change can be detected with 100 informal caregivers if the standard deviation (SD) of the change is around 14 [35, 36].

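### The 20% attrition allowance does not protect the 199 patients required, cannot include death over 36 months, and leaves 100 caregivers unsupported after about month 12

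*Protocol article*

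**What the plan says.** All of these statements are in the protocol article.

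- Sample size, primary outcome: the historical cohort is taken to average seven hospital days a year, and the authors "hypothesize that the intervention will cause a reduction of two days/year with an assumed SD of 7 days". This leads to 199 required participants, followed by: "With an estimated attrition rate of 20%, we aim to include 240 patients". The text does not say whether death counts as attrition, or over what period the 20% applies.
- Primary outcome: admissions are counted from the first visit until the patient dies or leaves the study, and are "compared to a recent historic cohort of a similar size from the involved centers".
- Sample size, opening sentence: the targets are 240 patients and "100 informal caregivers, based on sample size calculations for the most significant outcomes and to accommodate expected attrition". The caregiver calculation is a 5-point change on the Zarit Burden Interview (ZBI) with an SD of change of about 14. It gives no attrition rate and no visit.
- Introduction: on decompensation, "median survival decreases dramatically from approximately 12 years to just two years". The Abstract describes the eligible patients as decompensated.
- Intervention elements: after the first follow-up, conversations take place "at 6, 12, 18, 24, 30, and 36 months, or until withdrawal from the study or death". The ZBI is collected at baseline and before every planned visit.

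**The concern.** The allowance is meant to ensure that enough participants remain for the calculations to hold. Three things suggest that it does not.

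First, applying the stated loss to the stated target gives fewer patients than the same paragraph requires.

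Second, one undated 20% stands beside a two-year median survival and follow-up of up to three years. If the 20% is read as loss from all causes, the two cannot both be right.

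Third, the caregiver target is said to allow for attrition, yet whether 100 is enough depends on the visit at which change is judged, and the calculation names none. A reader could take the trial to have good power for caregiver change at every visit to month 36.

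**Working it through.** **1. Reproducing 199 and 240.** Inputs from Sample size: difference 2 days/year, SD 7. Alpha and power are not stated; two-sided 0.05 and 80% are assumed. The historic cohort is of similar size, so 1:1.

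- Normal formula: n per group = 2 × (1.960 + 0.842)² × 7² / 2² = 192.3, so 193. The t-test version gives 194. The stated 199 is within 3% of this as a per-group number. As a total for two groups, 199 would have only 52% power, so the per-group reading is used.
- 199 × 1.2 = 238.8, which explains 240.

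**2. Does 240 protect 199?**

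- 240 × (1 − 0.20) = 192, which is less than 199.
- Correct inflation: 199 / (1 − 0.20) = 248.75, so 249.
- Largest loss that 240 can absorb: 1 − 199/240 = 17.1%.
- Two-sample t-test power: 81.1% at 199 per group and 79.7% at 192 per group.

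**3. Can 20% include death?** Input: median 24 months (Introduction). Assumption: exponential survival, S(t) = 0.5^(t/24).

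- 20% dead when 0.5^(t/24) = 0.8, so t = 24 × ln 0.8 / ln 0.5 = 7.7 months.
- Deaths by 12, 24 and 36 months: 1 − 0.707 = 29%, 1 − 0.500 = 50%, 1 − 0.354 = 65%.
- Range: at 36 months, deaths are 50% with a 36-month median and 41% with a 48-month median. For only 20% dead at 36 months, the median would have to be 36 × ln 0.5 / ln 0.8 = 112 months.

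**4. Caregivers.** Inputs: 100 caregivers, change 5, SD of change 14. Assumptions: paired t-test, two-sided 0.05, caregiver lost when the patient dies, no other loss. The noncentrality is (5/14) × √n. Power is 94% at n = 100, and 80% needs n = 64.

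| Month | S(t) | Caregivers left of 100 | Power |
|---|---|---|---|
| 6 | 0.841 | 84 | 90% |
| 12 | 0.707 | 71 | 84% |
| 18 | 0.595 | 59 | 77% |
| 24 | 0.500 | 50 | 70% |
| 36 | 0.354 | 35 | 54% |

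The number left falls below 64 between months 12 and 18. If a further 20% withdrew (an illustration; the article gives no caregiver rate), month 6 would have 100 × 0.841 × 0.8 = 67 caregivers and 82% power, and month 12 would have 100 × 0.707 × 0.8 = 57 and 75%.

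**The case against.** The strongest reply is that the 20% was never meant to include death. It is applied only to the hospital-days calculation, where death ends observation without making the outcome missing, and the visit schedule lists withdrawal and death as separate events. The two-year median is background in the Introduction, not a planning assumption, and the sources cited for the 20% are not available here. This stands as far as it goes: read as withdrawal, 20% does not conflict with the survival figure. But the article does not say so, and the other reading fails by a wide margin even at a 48-month median.

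A second reply is that the shortfall of 192 against 199 hardly matters. That is right about size, a little over one percentage point of power. The paragraph still states a requirement that its own allowance does not meet.

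A third is that 100 caregivers exceed the 64 needed, that no power is claimed at months 24 to 36, and that the visit for a secondary outcome may be left to the full protocol or analysis plan. The number is indeed adequate early on, and a missing visit alone would be no finding. However, the article itself says that 100 allows for attrition, and that holds at some of its planned visits and not at others.

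**Conclusion.** The point holds in three limited parts.

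- **Arithmetic.** 240 less 20% is 192, not 199. This follows from the article alone. Its cost in power, about 81% to 80%, rests on 199 being per group with two-sided alpha 0.05.
- **Meaning of the 20%.** It cannot include death over 36 months at the stated median, so for the primary outcome it is tenable only as withdrawal. This rests on exponential survival and on the Introduction's figure applying to the enrolled patients. Medians of 36 and 48 months lead to the same conclusion.
- **Caregivers.** 100 is supported to about month 12 and not at later visits, if caregiver loss follows patient death and there is little other loss.

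Three stronger conclusions might be inferred, and the documents do not support them:

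- That mortality cuts the primary-outcome sample to the roughly 85 patients (240 × 0.354) alive at month 36. Patients who die contribute their admissions and time up to death.
- That unequal follow-up lowers primary power by a known amount. Any such figure depends on how the days are annualised and weighted and on the pattern of admissions, none of which the article states.
- That the numbers are wrong for PRO-Pall and EQ-5D-5L. The article gives no sample size calculation for either, and it never applies the 20% to caregivers.

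**What to change.** Reword the Sample size section in three places:

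1. Correct the inflation. Either give the evaluable number as 192 with its power, or keep 199 and give the tolerable loss as 17%.
2. State that the 20% is withdrawal only, and that patients who die contribute time at risk to the primary outcome up to death.
3. Tie the 5-point ZBI calculation to one early visit, month 6 or month 12. Give the number of caregivers expected to be evaluable there after both death and withdrawal, and make no power claim for later visits. If withdrawal on top of death is expected to be near 20%, month 6 keeps power above 80% and month 12 does not.

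The cost is that the stated figures become slightly less favourable. No extra patients or caregivers are needed.

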### Statistical methods

All data will be entered into a shared REDCap database [42]. Descriptive statistics for numerical data will be presented as means with standard deviations (SD) for normally distributed variables, or as medians with interquartile ranges (IQR) for non-normally distributed variables. Categorical data will be presented as counts and proportions. For between-group comparisons, unpaired two-sample Student’s *t*-tests will be used for normally distributed numerical data, and the Wilcoxon-Mann-Whitney test for non-normally distributed numerical data. Categorical variables will be compared using the chi-squared test. Differences between groups will be reported as means with standard errors (SE) and 95% confidence intervals (CI) for numerical outcomes, and as odds ratios (OR) with 95% CI for dichotomous outcomes. All statistical analyses will be conducted using Stata Statistical Software, version 16 (StataCorp, College Station, Texas). Missing data will be reported and explored. Where appropriate, multiple imputation techniques will be considered. Both intention-to-treat (ITT) and per-protocol analyses will be conducted to assess robustness of findings.

The cost-effectiveness analysis will include cost and effect. The costs will include intervention-related expenses (e.g. staff time, training, materials) while the effect will include the use of healthcare resources using Danish DRG standard tariffs.

The cost-utility analysis will be based on the EQ-5D-5 L-data and the values will be converted to utility scores using Danish population-based value [43]. These scores will be used to estimate QALYs, which will serve as the measure of effectiveness.

The qualitative analysis will follow a systematic approach inspired by content analysis as described by Graneheim and Lundman [44]. An initial overview of each transcript will be obtained through repeated reading. Subsequently, each patient’s experiences and interpretations will be analysed line by line to identify meaning units. Relevant meaning units will be selected, condensed, and coded to reflect the content while preserving context. Codes will be sorted into mutually exclusive categories and subcategories, comparing and describing different experiences regarding knowledge needs across disease etiology and severity [44]. NVivo software (NVivo qualitative data analysis software; QRS International Pty Ltd. Version 12, 2018) is used for the initial sorting of data. The analytical process will alternate between software-based and manual processing to facilitate data management and ensure a comprehensive overview. All categories and meaning units will be re-examined to ensure validity and consistency across the dataset.

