## Method

### Study setting

The LiverCare study is conducted in four hepatology departments covering three of the five regions of Denmark. The hospitals include Copenhagen University Hospital Amager Hvidovre and Copenhagen University Hospital Herlev Gentofte placed in the Capital Region, University Hospital of Southern Denmark, Esbjerg placed in the Region of Southern Denmark, and Aarhus University Hospital in the Central Denmark Region.

The four hospitals comprise a catchment area of 1.6 million citizens, approximately 27% of the Danish population.

In Denmark, all residents have universal, tax-funded access to healthcare services, including general practitioners and specialized hospital care. The healthcare system is organized into a primary sector (general practitioners and municipal health services) and a secondary sector (hospital-based care) [25].

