### Phase 1: education of health care professionals

All healthcare professionals involved in the palliative care intervention attend a specially designed one- or two-day course with a focus on theoretical and practical education and training within palliative care, communication, thorough symptom assessment, PRO-PALL questionnaire [31], ACP, and the 4-2-4-2 model [29, 32]. The education and training were facilitated by palliative care experts and professional actors.

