### Phase 3: intervention study

A total of 240 patients and possible informal carergivers will participate in the palliative care intervention. The intervention will be initiated following completion of Phase 2, incorporating any adjustments identified during the feasibility phase.

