The inclusion of an initial feasibility study further strengthens the overall study design and reflects the MRC framework’s recommendation to assess feasibility before conducting a full evaluation of complex interventions [23]. Feasibility testing allows us to assess acceptability, fidelity, recruitment pathways, workflow, and data-collection procedures before launching the full trial [47]. These insights will guide refinements of both the intervention and implementation strategy, thereby reducing the risk of attrition, non-adherence, and site-level variation later in the study. Taken together, the feasibility phase and process evaluation increase the likelihood that the intervention will be not only effective but also implementable and scalable.

The multicenter design enhances generalisability but introduces the possibility of variability in prerequisites between sites in terms of culture, staffing, resources, and local workflows. Such heterogeneity may affect fidelity and complicate interpretation of outcome data [23]. The process evaluation is therefore crucial in documenting contextual influences and enabling nuanced understanding of how and why outcomes differ across settings. This knowledge is essential for future scale-up beyond the study sites.

The results of the LiverCare study will be disseminated in peer-reviewed journals and at national and international conferences. Findings will inform clinical practice and support education and competence development for healthcare professionals working with advanced liver disease. Insights will also guide future implementation strategies and contribute to strengthening palliative care provision within hepatology.

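### The named between-group tests ignore centre, although the two cohorts are two periods within the same four departments

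*Protocol article*

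**What the plan says.** - **Setting (Study setting):** "The LiverCare study is conducted in four hepatology departments covering three of the five regions of Denmark".
- **Delivery (Phase 1):** "All healthcare professionals involved in the palliative care intervention attend a specially designed one- or two-day course". The intervention therefore reaches patients through trained department staff.
- **Timing (Phase 3):** "The intervention will be initiated following completion of Phase 2, incorporating any adjustments identified during the feasibility phase".
- **Comparator (Primary outcome):** utilisation is "compared to a recent historic cohort of a similar size from the involved centers". Size and source of the historic cohort are fixed; the share from each centre is not.
- **Tests (Statistical methods):** "For between-group comparisons, unpaired two-sample Student’s" t-tests are named for normally distributed numerical data, "and the Wilcoxon-Mann-Whitney test for non-normally distributed numerical data". Differences are to be reported with standard errors and 95% confidence intervals. No centre term or stratification is mentioned.
- **Sample size:** for a reduction of 2 days per year with SD 7, "Hence, 199 participants are required (STATA BE 18.5"). No design effect is mentioned.
- **Discussion:** the multicentre design "introduces the possibility of variability in prerequisites between sites in terms of culture, staffing, resources, and local workflows". The article says this may complicate interpretation of outcome data and leaves it to the process evaluation.

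**The concern.** Intervention patients come from the later period in each department and controls from the earlier one. The data are four centres by two periods, and the treatment contrast is the period contrast within centres. Two problems follow for a test that ignores centre.

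First, a similar overall size does not guarantee a similar centre mix. If one department supplies a larger share of one cohort, its usual level of bed use enters the estimate as if it were an intervention effect.

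Second, even with identical mixes, departments may change differently between periods, for instance through bed capacity or local discharge practice. Such changes enter the pooled difference with only four replicates, and a patient-level standard error leaves them out. A shift at one or two hospitals could then produce a significant pooled result for the primary outcome.

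**Working it through.** **The plan's own figure.** Inputs from Sample size: difference 2 days, SD 7. Two-sided 5% and 80% power are assumed, because the article states neither. n per group = 2 × (1.96 + 0.842)² × 7² / 2² = 192.3, so 193, or 194 with the t distribution. The stated 199 is within 3% of this as a per-group figure (power 81%); read as a two-group total it would give 52% power. Since 199/194 = 1.03, the figure leaves almost no room for a design effect.

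**Centre-specific change between periods.** Let ρ be the share of total variance due to centre-by-period variation. The article does not give it, so it is assumed. Take equal recruitment (also assumed) and 240 patients less 20% attrition: 192 per group, m = 48 per centre and period.

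- Standard error used by the test: 7 × √(2/192) = 0.714 days.
- Design effect: DE = 1 + (m − 1)ρ.
- True standard error: 0.714 × √DE.
- Actual two-sided type I error: 2Φ(−1.96/√DE).

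| ρ | SD between centre-periods, 7√ρ (days) | DE | True SE (days) | Type I error | Coverage of 95% CI |
|---|---|---|---|---|---|
| 0 | 0 | 1.00 | 0.71 | 5.0% | 95% |
| 0.01 | 0.70 | 1.47 | 0.87 | 10.6% | 89% |
| 0.02 | 0.99 | 1.94 | 1.00 | 15.9% | 84% |
| 0.025 | 1.11 | 2.18 | 1.05 | 18.4% | 82% |

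At 199 per group the rates for ρ = 0.01 and 0.02 are 10.8% and 16.3%; at 240 per group they are 12.0% and 18.4%. Simulation with 50 patients per centre and period gives 10.3% (t-test) and 9.4% (Wilcoxon) at ρ = 0.01, and 16.7% and 15.9% at ρ = 0.02. The rank test does not avoid the problem.

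**Stable centre differences, same mix.** With a constant centre share of 5% of variance and no centre-by-period part, simulated type I error is 4.7% for both tests. There is no inflation.

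**Stable centre differences, unequal mix.** Assume 80/60/32/20 patients by centre in one cohort, 48 each in the other, and a constant centre share of 5%.

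- Differences in centre weight: 0.167, 0.063, −0.083, −0.146; sum of squares 0.0599.
- Variance from centre mix: 0.05 × 49 × 0.0599 = 0.147.
- Variance from patients: 0.95 × 49 × 2/192 = 0.485.
- True SE: √0.632 = 0.795, against 0.714 assumed by the test.
- Type I error: 2Φ(−1.96 × 0.714/0.795), about 8%. Simulation gives about 8.5% for the crude t-test and 5% with centre fitted.

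**What fitting centre does not do.** With equal mix and ρ = 0.01, the fixed-centre model still rejects in about 11 to 12% of simulated null trials.

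**Inference on the four centre differences (t, 3 df).** This holds the 5% level, but at 192 per group its power for 2 days is about 48% at ρ = 0 and 36% at ρ = 0.01.

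**The case against.** **The inflation rests on an assumed variance.** This stands. The article gives neither an intraclass correlation nor a centre-by-period variance, and the true value could be near zero. The rates are a range, not an estimate.

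**The Discussion does not show the mechanism.** This also stands. A reader might take its remark on site variability as evidence that centres drift apart over time. It describes differences between sites, which largely cancel when the same centres supply both cohorts in similar proportions.

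**No department-by-department rollout is described.** A reader might infer a staggered start from four departments training their staff. Phase 3 says only that the intervention starts after the feasibility phase; patients are then invited individually and consent. Delivery at department level is all that the documents support, and all that the calculation uses.

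**The tests are generic, and a full analysis plan may add centre.** This stands in part. Statistical methods lists tests by data type and designates no primary model. But those are the only tests given for numerical between-group comparisons, and a centre-adjusted analysis would depart from them.

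**Treating four centres as random replicates is debatable.** Agreed. With about 36 to 48% power, a 3-df interval could be inconclusive even if the hypothesised effect is real, so it should not be the primary analysis.

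**Common trends and patient selection are larger threats.** They may be. They are sources of bias that no centre term removes, but that is no reason to leave centre out.

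**Conclusion.** The point holds in a limited form. Group coincides with period within four centres, the named tests have no centre term, and the sample size shows no allowance for clustering. Unequal centre mix can distort the comparison: in the assumed example the crude test has about 8 to 9% false positives, against 5% with centre fitted. Centre-specific change may make the pooled interval and p-value too optimistic: about 5% false positives with none, about 10% at 1% of total variance, and 16 to 18% at 2 to 2.5%. These figures assume SD 7, normal data, equal recruitment (except in the mix example) and a two-sided 5% level.

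A reader might conclude that the stated test is shown to be invalid. The documents do not support that: they give no evidence that the departments change differently between periods. The case for change is that a better comparison is cheap and would show whether one hospital drives the result.

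**What to change.** 1. **Primary outcome:** draw the historic cohort in the same centre proportions as the intervention cohort.
2. **Statistical methods:** include centre as a fixed effect in the primary comparison.
3. Report the intervention-minus-historic difference, with its interval, for each of the four centres.
4. State that the pooled interval assumes no centre-specific change between periods.
5. Optionally, add an interval from the four centre differences (t, 3 df) as a sensitivity analysis, noting its low power.

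Steps 1 and 2 deal with centre mix. Steps 3 and 4 disclose centre-by-period variation but do not correct for it. None of the steps removes a time trend common to all centres.

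**Cost:** no new patients or visits. Step 1 is a design decision, since it constrains sampling of the historic cohort by centre; the rest is analysis and reporting text. A significant pooled result may need more cautious wording if the four differences disagree.
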